## Abstract

**Background:**

Parkinson’s disease (PD) is a neurodegenerative disorder characterized by postural instability, which significantly contributes to an increased risk of falls (occurring in 45–68% of persons with PD annually), leading to greater functional dependence, social isolation, and a significant decrease in quality of life. The aim of this randomized clinical trial is to evaluate the effects of an immersive virtual reality (IVR) intervention on static and dynamic balance, gait speed, functional mobility, lower limb strength, and quality of life in people with PD. Furthermore, the study will assess treatment adherence, participant satisfaction, as well as the potential occurrence of adverse effects associated with the application of IVR.

**Methods:**

A 10-month, single-blind, two-arm randomized controlled trial will be conducted with participants aged 55–90 years diagnosed with PD and classified between stages 2.5 and 4 on the modified Hoehn and Yahr scale. Participants will be randomly assigned to one of two groups: an experimental group and a control group. The intervention will consist of an 8-session program. The first part of each session, common to both groups, will include a standardized strength training program. In the second part, the experimental group will receive a physical therapy balance program using IVR, while the control group will follow a usual physical therapy balance exercise program.

**Discussion:**

This study will examine whether IVR can improve static and dynamic balance rehabilitation in Parkinson’s disease beyond usual physical therapy, addressing real-world motor and dual-task challenges. By providing enriched sensory input and adaptive tasks, the IVR seeks to optimize motor learning and functional mobility. Demonstrating safety and clinically meaningful improvements would support IVR as a scalable and engaging tool to reduce risk of falls and enhance quality of life in PD.

**Trial registration:**

ClinicalTrials.gov NCT07274514

## Introduction

Parkinson’s disease (PD) is the second most prevalent neurodegenerative disorder. Its incidence is estimated to range from 5 to 35 cases per 100,000 people, with a marked increase observed with advancing age, rising by 5- to 10-fold between ages 60 and 90 [1]. The number of individuals diagnosed with PD worldwide is expected to reach approximately 1.93 million by 2030, with age-adjusted incidence rates projected to be 27 per 100,000 population [2]. Although the exact etiology remains unclear, PD is considered a multifactorial condition resulting from complex interactions between genetic and environmental factors. Genetic components are estimated to account for approximately 5–10% of cases [3–5]. Additionally, exposure to environmental risk factors, including toxins, pesticides, bacteria, and viruses, has been associated with an increased likelihood of developing PD, possibly due to inflammatory responses mediated by microglial activation [4].

PD is primarily characterized by the progressive degeneration of dopaminergic neurons in the substantia nigra, a critical component of the basal ganglia circuitry. This neurodegeneration leads to reduced dopamine levels, resulting in impaired motor control and disrupted communication between the basal ganglia and other regions of the central nervous system (CNS), such as the motor and premotor cortices [6]. The reduction in dopaminergic input also triggers compensatory changes in other neurotransmitter systems, particularly increased cholinergic and glutamate activity. These changes disturb the neurochemical balance within the striatal pathways, compromising the precise regulation of motor functions and contributing to the development of PD symptoms [7].

The clinical manifestations of PD include both motor and non-motor symptoms, usually appearing around 60 years of age, although early-onset cases also occur [8]. Non-motor symptoms, which often precede motor signs by up to 10 years, are attributed to the involvement of other CNS regions, including the nucleus basalis of Meynert, olfactory bulb, dorsal motor nucleus of the vagus, and peripheral autonomic ganglia and pathways [9,10]. These symptoms encompass neuropsychiatric disturbances [8,9,11]; autonomic dysfunction [9,10]; and oculomotor abnormalities [10,12]. Motor impairments typically involve resting tremor, rigidity, bradykinesia, postural instability, and gait abnormalities [5]. These clinical manifestations are often exacerbated by increased muscular stiffness in the trunk and extremities, which further contributes to postural dysfunction and balance impairments. These issues significantly affect daily functioning [13] and lead to abnormal postural and movement patterns, resulting in deficits in both static and dynamic balance. Postural instability and gait disturbances usually develop between 10–15 years after the onset of PD and are among its most disabling manifestations. In particular, postural instability is a major source of morbidity, as it frequently leads to recurrent falls (occurring in 45–68% of patients with PD annually) [14,15] reduced functional independence, and social isolation [1]. These consequences contribute to a decline in quality of life and place a considerable burden on caregivers and healthcare systems [14].

While pharmacological treatments, such as levodopa and dopamine agonists, and surgical options like deep brain stimulation, can alleviate some symptoms [11,16,17], their efficacy tends to decrease over time, and they do not prevent disease progression [18]. Therefore, complementary therapies, including physical therapy, play a crucial role in the long-term management [18–22]. Usual physical therapy interventions targeting motor function, particularly balance, gait, and postural control, have demonstrated meaningful clinical benefits in individuals with PD [19,21–23]. In recent years, digital health technologies such as virtual reality (VR) have emerged as promising tools to enhance rehabilitation outcomes [24]. VR-based interventions enable patients to engage in interactive, task-specific exercises within a controlled virtual environment, stimulating both cognitive and motor functions. These systems vary in their level of immersion: non-immersive VR (NIVR) typically involves screen-based interactions with limited sensory feedback; semi-immersive VR (SIVR) offers greater spatial interaction while maintaining awareness of the real world; and immersive VR (IVR) provides a fully immersive experience via head-mounted displays and motion sensors, allowing real-time interaction with a 3D virtual environment [25]. Beyond its technological characteristics, IVR may influence balance control through specific sensorimotor and cognitive mechanisms. Balance impairments in PD are not only related to musculoskeletal deficits but also to altered sensory integration and delayed motor responses to external perturbations. In this context, Campo-Prieto et al. [26] reported that reaction time measured in immersive virtual environments was associated with fall risk in people with PD. These findings suggest that IVR tasks challenging rapid visuomotor responses and sensorimotor integration may target processes that are also fundamental to postural control and fall prevention [26].

Evidence also suggests that VR interventions can improve PD rehabilitation by enhancing balance and gait speed, as well as improving motor function and quality of life [13,27–30].

Despite these promising findings, research specifically evaluating the impact of IVR on static and dynamic balance in PD remains limited [31]. Therefore, the primary aim of this study is to evaluate the effects of an IVR physical therapy program on static and dynamic balance improvement in individuals with PD. Additionally, it will explore its effects on gait speed, functional mobility, lower limb strength, and overall quality of life. Furthermore, potential adverse events associated with IVR use and participants’ satisfaction with the intervention will be monitored.

## Materials and methods

### Study design

This protocol has been designed according to the Standard Protocol Items: Recommendations for Interventional Trials (SPIRIT). Two parallel interventions will be compared: an experimental group receiving an IVR physical therapy program to improve static and dynamic balance in different tasks in people with PD, and a control group receiving a usual physical therapy balance exercise program.

Recruitment for this randomized controlled trial began on February 5, 2025. Participant recruitment is ongoing and is expected to be completed at the end of February 2026. Data collection is anticipated to be completed by May 2026, and publication of results is planned by the end of 2026 (Fig 1 and Fig 2). This trial protocol has been reviewed and approved by the Ethics Committee of Aragón (reference number: PI24/501) and prospectively registered at ClinicalTrials.gov (NCT07274514).

**Fig 1 pone.0344457.g001:**
[figure not shown]
SPIRIT schedule enrollment.

**Fig 2 pone.0344457.g002:**
[figure not shown]
Flowchart.

Figs 1 and 2 illustrate the design of the clinical trial.

### Setting and population

The study will be conducted with people diagnosed with PD at the Aragon Parkinson’s Association in Zaragoza, Spain. Recruitment will be carried out by the physical therapy association team, who will identify eligible candidates during their physical therapy sessions.

### Eligibility criteria

Before inclusion in the study, all potential participants will be fully informed about the study and asked to provide written informed consent. The inclusion criteria will be: 1) Patients diagnosed with PD by a neurologist; 2) Aged 55–90 years and classified as stages 2,5–4 on the modified Hoehn & Yahr scale; 3) Independent in standing and walking, with or without technical aids; 4) A score >24, as evaluated using the validated Spanish version of the Mini-mental State Examination (MMSE-MEC) [32]. The exclusion criteria included will be: 1) Visual or auditory disturbances that make it difficult to perceive the information provided or may cause vertigo or epilepsy; 2) Musculoskeletal disorders or pathological conditions limiting the ability to perform exercises; 3) Psychiatric disorders such as moderate or severe depression, as well as impulse control disorders diagnosed in the last year. The withdrawal criteria will be: 1) Occurrence of severe adverse effects during IVR use, defined as a Simulator Sickness Questionnaire (SSQ) score greater than 20; 2) Voluntary withdrawal by the participant.

### Allocation and blinding

Recruited patients will be randomly assigned to one of the two groups after the baseline evaluations. The sequence will be randomized, with a 1:1 allocation using randomization software (www.randomizer.org) between the experimental and the control group. Each participant will receive an identification code to ensure anonymity. Randomization will be conducted by an independent researcher who is not involved in the treatment or assessment. Outcome assessments will be performed by an evaluator blinded to group assignment, and the research team delivering the intervention will be excluded from all assessment activities to ensure a single-blind design.

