### Procedure

Once potential participants are recruited by the physical therapy association team, the research team will provide them with detailed information about the study’s objectives. Individuals who potentially meet the inclusion and exclusion criteria will be preselected for participation. Participants who agree to participate will be asked to provide written informed consent. A trained researcher with expertise in neurological assessment will schedule each enrolled participant for the baseline evaluation. All assessments will be conducted by the same evaluator and in the same facility at the Parkinson’s Association of Aragón to ensure consistency in testing conditions. Each evaluation session will last approximately 60 minutes.

After the initial assessments, participants will be randomly assigned to either the experimental or control group. Participants will be instructed not to disclose their group assignment to the evaluator during follow-up assessments to minimize potential bias. Intervention in both groups will be administered by 3 physical therapists, each with at least 2 years of experience managing patients with neurological conditions. To ensure consistency and adherence to the study protocol, all therapists will attend a training session focused on standardizing the intervention procedures. Additionally, they will be provided with detailed written guidelines for the intervention. This process will be implemented to ensure consistent patient management across physical therapists and to facilitate accurate documentation of any adverse events that may occur during the intervention.

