### Sample size calculation

Sample size estimation was performed using G*Power software (version 3.1.9.7), taking the primary outcome variable, balance, assessed by the Mini-BESTest scale as the reference. Although the hypothesis anticipates superior outcomes for the experimental IVR intervention compared to the control condition, a two-tailed alternative hypothesis was adopted to maintain a conservative statistical approach. The calculation was based on a repeated measures design involving two groups and three time points, but specifically on the expected difference between groups at the post-intervention time point assuming a moderate effect size (d = 0.71), a significance level of 0.05, and a statistical power of 80%**.** Although the study includes follow-up measurements, this approach provides a conservative estimate expected to offer adequate power for comparisons at follow-up. Because the sample size calculation relies on the expected between‑group difference at the post‑intervention time point, assumptions about the correlation between repeated measurements will not be necessary. Under these conditions, the required sample size was determined to be 50 participants, with 25 allocated to each group. To accommodate an estimated 10% attrition rate, the final target sample was increased to 56 participants (28 per group).

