### Statistical analysis

Statistical analysis will be performed with Statistical Package for the Social Sciences version 29.0 (SPSS Inc, Chicago, IL). The significance level will be 0.05 for all statistical analyses. Descriptive statistics will summarize participants’ baseline characteristics and study outcomes. Categorical variables will be presented as absolute and relative frequencies (n, %), whereas continuous variables will be expressed as mean ± standard deviation or, when appropriate, as median and interquartile range, together with 95% confidence intervals. The Shapiro–Wilk test will assess the normality of continuous variables. To ensure comparability between groups at baseline, appropriate parametric or nonparametric tests will be applied depending on data distribution: t-tests or Mann–Whitney U tests for continuous data, and Chi-square tests for categorical data.

To examine the effects of the intervention across time, linear mixed-effects models will be employed to analyze group‑by‑time interactions across the three measurement points. Significant main or interaction effects will be further explored through Bonferroni-adjusted post hoc comparisons. In cases where data deviate from normality, within-group changes will be analyzed using the Friedman test, followed by Wilcoxon signed-rank tests for pairwise comparisons. Bonferroni correction will be applied to control for multiple testing and Type I error.

Between-group differences at each time point will be examined using independent-samples t-tests (accompanied by Levene’s test for homogeneity of variances) for normally distributed data, or Mann–Whitney U tests for non-parametric data. Categorical outcomes will be compared using Chi-square or Fisher’s exact test, as appropriate.

All analyses will follow the intention-to-treat (ITT) principle, including every randomized participant in the group to which they were initially assigned, regardless of adherence, or protocol deviations. Missing data will be managed through suitable statistical procedures, such as last observation carried forward (LOCF) or multiple imputation, depending on the type and extent of missingness.

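### The post-intervention Mini-BESTest comparison that sizes the trial is tested without adjustment, although stages 2.5 to 4 are admitted and no stratification by stage is named

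*Protocol article*

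**What the plan says.** **Eligibility criteria** admits participants "classified as stages 2,5–4 on the modified Hoehn & Yahr scale", so stage is known for everyone at entry.

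**Allocation and blinding** places randomization after the baseline evaluations and describes it thus: "The sequence will be randomized, with a 1:1 allocation using randomization software (www.randomizer.org) between the experimental and the control group". It adds: "Randomization will be conducted by an independent researcher who is not involved in the treatment or assessment". No stratification factor is named.

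**Sample size calculation** is built on the expected between-group difference at post-intervention, with d = 0.71, two-tailed 0.05 and 80% power: "the required sample size was determined to be 50 participants, with 25 allocated to each group". The total is raised to 56 for 10% attrition.

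**Statistical analysis** has two layers. First, "linear mixed-effects models will be employed to analyze" group-by-time interactions over three measurement points. Second, the arms are compared at each time point by independent-samples t-tests or Mann-Whitney tests, with no covariate. If data are not normal, the stated alternative to the model is a within-group Friedman test, which leaves Mann-Whitney as the only between-group test described for the Mini-BESTest. Baseline characteristics are also tested between arms, but nothing is said to follow from the result.

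**Strengths and limitations** mentions adjustment for concurrent treatments only.

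**The concern.** The primary outcome is balance, and the admitted stages span a wide range of severity, so stage is likely to be related to the Mini-BESTest score. Stage is named neither as a stratification factor nor as a covariate in the comparison that fixes the sample size. If one arm happens to receive more stage 4 participants, the post-intervention difference carries that imbalance, and a reader cannot separate it from the treatment effect. The baseline significance tests may flag such an imbalance but do not correct it.

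What is at stake is precision and how convincing a single small trial will be. The validity of the randomized test is not in question.

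**Working it through.** **1. The plan's own figure.** For a two-sample t-test with d = 0.71 and n = 25 per arm, the noncentrality is d√(n/2) = 0.71 × √12.5 = 2.51 on 48 df. Two-sided power is 69.1%; one-sided power is 79.7%. The stated 80% is thus met only by a one-sided test. That is a separate matter, and 69.1% is used below as the unadjusted reference. The inflation reproduces: 50/0.90 = 55.6, rounded up to 56.

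**2. How often the arms differ in severity.** The article gives no stage mix, so the stage 4 share is an assumption. The table gives the probability that the arms differ by at least 20 percentage points in stage 4 share.

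| Stage 4 among 56 (assumed) | Arms fixed at 28:28, no strata (hypergeometric) | Simple 1:1 allocation |
|---|---|---|
| 11 (20%) | 4.0% | 6.3% |
| 17 (30%) | 8.0% | 11.9% |
| 22 (40%) | 17.1% | 14.1% |

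The jump in the middle column reflects whole numbers: with 11 or 17 stage 4 participants the smallest qualifying difference is 7 people, with 22 it is 6. The point does not depend on which allocation method is used.

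**3. What an imbalance does to the unadjusted comparison.** Shift = difference in share × gap between stages. With 20 points and an assumed gap of 1 SD: 0.20 × 1 = 0.20 SD, and 0.20/0.71 = 28% of the planned effect. With gaps of 0.5 and 1.5 SD the shift is 0.10 and 0.30 SD, or 14% and 42%.

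**4. What it does to the group-by-time term.** Baseline, post-intervention and the 3-month follow-up make up the three measurement points. Write the score of participant i at time t as group-time mean + β × stage + person effect + error. With complete data the interaction estimate for post-intervention is the mean change in one arm minus the mean change in the other. β × stage is the same at both times, so it cancels. I checked this on one invented data set (56 people, 17 at stage 4, random-intercept model). The interaction estimate was 0.222 with SE 0.192, both with and without a stage main effect. The SE of the group contrast at a single time point fell from 0.243 to 0.214 when stage was added. A stage main effect therefore helps only the contrast at a time point.

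**5. What adjustment gains for the post-intervention contrast, at 25 per arm.** If stage explains R² of outcome variance, the effective effect size is 0.71/√(1 − R²).
- R² = 0.10 (assumed): 0.71/√0.90 = 0.748, power 73.6% (47 df).
- R² = 0.25 (assumed): 0.71/√0.75 = 0.820, power 81.0%.

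Now put baseline Mini-BESTest in first, with an assumed correlation ρ between baseline and post-intervention scores. Residual variance becomes 1 − ρ². If stage is equally correlated with both scores, its remaining share is R²(1 − ρ)/[(1 − R²)(1 + ρ)].

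| ρ (assumed) | Baseline only | Plus stage, R² = 0.10 | Plus stage, R² = 0.25 |
|---|---|---|---|
| 0.5 | 81.0% | 82.4% | 85.3% |
| 0.6 | 86.7% | 87.6% | 89.4% |
| 0.7 | 93.1% | 93.5% | 94.4% |

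Adjusting for baseline gives the main gain. Stage then adds 0.4 to 4.3 points across the table, and less than 3 points when ρ is 0.6 or more.

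**The case against.** The strongest reply is that chance imbalance does not bias a randomized comparison, that its contribution is already in the test's standard error, and that covariate lists are commonly left to an analysis plan that is not shown. The first two parts stand: type I error is not at issue, and on the assumptions above most trials would not reach a 20-point imbalance. The third stands only in part. The article does not leave this comparison open. It specifies unadjusted tests at each time point, and the sample size rests on one of those contrasts.

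The reply that baseline is already in the mixed model also stands for the group-by-time term. It does not extend to the separate tests at each time point.

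A reader might infer more than the article supports:

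- **That the sequence is simple or unrestricted.** The article says neither simple nor blocked, and it plans 28 per group. A condensed article may leave block details to the full protocol.
- **That unequal arms undermine the sample size.** Even under simple allocation this is nearly nil. Two-sided power is 74.2% at 28:28 and 73.3% at 24:32, both above the 69.1% at 25:25. Only 18:38 or worse falls below 25:25, with probability 1.0%.
- **That therapist is confounded with arm.** The same three therapists treat both groups after common training and with written guidelines. No rule assigning participants to therapists is described, so neither an imbalance nor its size can be derived.

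**Conclusion.** The concern holds for one analysis: the unadjusted between-group Mini-BESTest tests, above all at post-intervention. With no stratification by stage named and no covariate in those tests, a severity imbalance passes directly into the estimate. Given 20-40% at stage 4 and a gap of 0.5 to 1.5 SD, an imbalance of 20 points or more has a probability of 4-17%, and a 20-point imbalance moves the estimate by 0.1 to 0.3 SD. The stage mix, the gap, R² and ρ are all assumptions; the article gives none of them.

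The concern does not hold for the group-by-time term, where stable stage differences cancel. It is not a claim of bias, and it gives no reason to alter the allocation list. This is a modest improvement to precision and credibility that costs almost nothing.

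**What to change.** Before any outcome data are analyzed, replace the unadjusted Mini-BESTest tests at post-intervention and follow-up with an adjusted between-group contrast. For example: *The between-group difference in Mini-BESTest at post-intervention and at the 3-month follow-up will be estimated with its 95% confidence interval from a mixed model (or ANCOVA at each time point), with baseline Mini-BESTest and Hoehn and Yahr stage at entry (2.5-3 versus 4) as covariates. These covariates are included whatever the baseline comparisons show.*

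Adding stage as a main effect to the existing group-by-time model would not achieve this, because it leaves the interaction unchanged.

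The cost is one or two degrees of freedom and a dated change to the analysis text. Both covariates are already collected for every participant, including those already randomized, so no new patients, visits or measurements are needed. If only one covariate is kept, it should be baseline Mini-BESTest.
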